### 3.3 BIOCHEMICAL AND HAEMATOLOGICAL OUTCOMES:

#### i. **Blood Glucose Levels:**

- a. **Outcome Measurement:** Change in glycosylated hemoglobin and random blood sugar levels.
- b. **Justification:** Indicates metabolic health and risk for conditions like diabetes.

#### ii. **Lipid Profile:**

- a. **Outcome Measurement:** Changes in LDL, HDL, Cholesterol and triglycerides.
- b. **Justification:** Reflects cardiovascular health improvements.

#### iii. **Liver and Kidney Function Tests:**

- a. **Outcome Measurement:** Changes in enzyme levels (e.g., ALT, AST) and creatinine (along with eGFR).
  - b. **Justification:** Indicates improvements in organ function.
- iv. **Complete Blood Count (CBC):**
  - a. **Outcome Measurement:** Hemoglobin and hematocrit levels. Along with WBC ratios.
  - b. **Justification:** Indicates overall hematological health and potential for anemia improvement.
- v. **Micronutrient Levels:**
  - a. **Outcome Measurement:** Changes in Vitamin D, iron, and calcium levels.
  - b. **Justification:** Provides insight into nutritional and bone health improvements.
- vi. **Thyroid Function Tests:**
  - a. **Outcome Measurement:** Changes in TSH, T3, and T4 levels. Changes in testosterone, oestrogen and progesterone levels
  - b. **Justification:** Reflects endocrine health and potential metabolic improvements.

## 4 STUDY DESIGN

### 4.1 OVERALL DESIGN

This is a phase 3 cluster randomized, parallel arm, observer-blinded trial. The clusters will be urban Primary Healthcare Centres (PHCs- but also known as Health and Wellness Centres or Ayushman

Arogya Mandirs) in Bhubaneswar city, randomly assigned to either the Multi-FrAME intervention or standard care.

## 4.2 SCIENTIFIC RATIONALE FOR STUDY DESIGN

The use of a cluster randomized design is essential in this trial to effectively evaluate the Multi-FrAME intervention's impact within the urban Primary Healthcare Centres (PHCs) of Bhubaneswar city. Given the nature of the intervention, which includes various components at the healthcare center level, randomizing at the cluster level reduces contamination risks between participants receiving the intervention and those receiving standard care.

This design is particularly relevant in the context of Bhubaneswar's urban PHCs, where healthcare practices can vary significantly. By employing a cluster approach, the trial can assess the intervention in a way that mirrors real-world application, enhancing external validity. Randomization at the PHC level allows for the capture of data reflecting the complex interactions and systemic changes induced by the intervention. This will also improve future possibility of uptake into systems as the intervention is being tested at the point of proposed delivery through the system.

The observer-blinded aspect of the study further strengthens its validity by reducing assessment bias. Blinding ensures that outcome evaluators remain unaware of which group (intervention or control) the participants belong to, thus minimizing potential biases in data collection and interpretation.

## 4.3 JUSTIFICATION FOR INTERVENTION

The Multi-FrAME package is designed to address the multifaceted challenges posed by multimorbidity and frailty among older adults, conditions prevalent in the urban population of Bhubaneswar. Traditional care models often fall short in managing these issues comprehensively.

The intervention includes integrated components: medical management, nutritional support, tailored physiotherapy, structured physical activity, and psychosocial counselling. These elements are combined to provide holistic care that aims to enhance health-related quality of life, reduce healthcare utilization, and improve overall health outcomes.

By implementing this intervention at the PHC level, the trial leverages existing healthcare infrastructure, promoting sustainability and scalability. The Multi-FrAME package is expected to equip healthcare providers with the necessary tools to deliver patient-centered care that is customized to meet the specific needs of older adults with multimorbidity and frailty, ultimately improving individual and population health outcomes.

The focus on holistic care is supported by evidence indicating that multidimensional interventions can lead to improved physical function, better management of chronic conditions, and enhanced mental well-being, thereby addressing gaps left by standard care practices.

#### 4.4 END-OF-STUDY DEFINITION

The study will conclude after the 12-month follow-up data collection for all participants. This will include data analysis and preparation of findings for dissemination.

## 5 STUDY POPULATION:

### 5.1 INCLUSION CRITERIA

- Adults aged 60 years and above.
- Patients with multimorbidity, defined by two or more chronic health conditions, as assessed by the MAQ-PC plus tool(Pati et al., 2016).
- Frailty index score of  $\geq 0.25$  (Ghosh et al., 2023).
- Residents of Bhubaneswar city.

### 5.2 EXCLUSION CRITERIA

- Severe cognitive impairment or dementia as determined by the DART (Dementia Assessment Rapid Test)(B & V, 2015).
- Bedridden patients.

- History of significant cardiac health problems- (disorders with specific requirement by clinicians to avoid Maximal and Sub-maximal physical activities)
- Grade III Osteoarthritis or other severe mobility impairments.
- Participants unable or unwilling to provide informed consent.

### 5.3 LIFESTYLE CONSIDERATIONS

Field investigators will assess lifestyle factors through comprehensive interviews and standardized questionnaires. Key areas to evaluate include:

- **Physical Activity Levels:** Use the International Physical Activity Questionnaire (IPAQ) to assess regular physical activities, including walking, household chores, and exercise routines.
- **Dietary Habits:** A 24-hour dietary recall will be conducted to understand nutritional intake. Investigators should focus on the consumption of fruits, vegetables, protein, calcium, and iron-rich foods.
- **Social Engagement:** Assess social interactions and support systems using instruments like the Lubben Social Network Scale. We will consider involvement in community activities and family support dynamics.

### 5.4 SCREEN FAILURES

Investigators will carefully document screen failures to ensure transparent reporting and allow for process improvements. Procedures include:

- **Initial Screening:** Conducted through interviews using the MAQ-PC plus tool and DART test.
- **Criteria Check:** Investigators will ensure each criterion is meticulously verified. Document reasons for exclusion, such as failing the frailty index threshold or positive dementia screening.

- **Data Recording:** We will maintain a log of screen failures for audit purposes, including demographic details and reasons for exclusion, without including identifiable information in analyses.

## 5.5 STRATEGIES FOR RECRUITMENT AND RETENTION

### Recruitment:

- **Partnerships:** Collaborate with local health workers and community leaders who are trusted by potential participants. We will make attempts to recruit participants in equal proportions from each gender and age groups.
- **Awareness Programs:** Organize sessions in local community centers to explain the study's benefits and procedures.
- **Informed Consent:** We will provide clear, simple explanations and answer questions to ensure participants fully understand the consent form. This will be done using vernacular languages (English, Odia or Hindi) and visual aids.

### Retention:

- **Regular Follow-up:** We will schedule regular check-ins through phone calls or home visits to maintain participant engagement.
- **Feedback Mechanisms:** We will use a telephone hotline to create channels for participants to express concerns or difficulties, ensuring timely resolution.
- **Transportation Assistance:** We would offer support for participants facing challenges in traveling to PHCs.
- **Reward Systems:** We would provide small incentives to cover loss of wages as per ethical norms and certificates of appreciation to acknowledge participation.

## 6 STUDY INTERVENTION(S) OR EXPERIMENTAL MANIPULATION(S)

### 6.1 STUDY INTERVENTION OVERVIEW

The Multi-FrAME package will be implemented at the cluster level across urban PHCs. It includes comprehensive components tailored for addressing multimorbidity and frailty:

- **Medical Management:** Regular review and optimization of medication regimens, as well as tools to improve medication adherence.
- **Nutritional Support:** Education on balanced diets and supplementation with Vitamin D3, iron, folic acid, calcium, and protein as needed.
- **Physiotherapy and Physical Activity:** Customized exercise programs focusing on resistance and aerobic activities.
- **Psychosocial Support:** Individual and group sessions to support mental health and enhance social connections. Health promotion materials provided for self-help.

## 6.2 ADMINISTRATION AND/OR DOSING

- **Intervention Delivery:** Conducted by trained healthcare professionals at participating PHCs, assisted by trained investigators from the study team.
- **Monthly Contact Sessions:** All testing, data collection, clinical management, physiotherapy, and physical activity reviews conducted during these sessions.
- **Health Diary:** Each participant will receive a "Health Diary," serving multiple purposes:
  - **Intervention Log:** Enables participants and caregivers to maintain a daily record, helping verify intervention fidelity.
  - **Documentation Hub:** A single point for filing lab reports and documenting other medications and health updates during the trial.
  - **Information, Education, and Communication (IEC):** Contains materials for health promotion, behavior change, and education. Participants can refer to these resources for ongoing learning and support.

| Intervention Category               | Specifications                                                                                                                                                           | Dose/Frequency                                                                                                                                                                                                               | Mode of Administration                      | Self-care/Caregiver Required                   |
|-------------------------------------|--------------------------------------------------------------------------------------------------------------------------------------------------------------------------|------------------------------------------------------------------------------------------------------------------------------------------------------------------------------------------------------------------------------|---------------------------------------------|------------------------------------------------|
| Medical Management                  | Medication review and optimization; Diary for improving adherence and compliance                                                                                         | Monthly, with diary data being updated daily                                                                                                                                                                                 | In-person at PHC                            | Self-care, with caregiver assistance if needed |
| Nutritional Support                 | Vitamin D3, iron, folic acid, calcium, and protein supplements                                                                                                           | Doses are subject to the results of participants' biochemical tests for the respective nutrients. These doses will be monitored and modified as necessary to maintain nutrient levels within the biological reference range. | Oral supplementation                        | Self-care                                      |
| Physiotherapy and Physical Activity | Customized exercise program                                                                                                                                              | Monthly sessions, with daily exercises                                                                                                                                                                                       | In-person sessions and home-based exercises | Self-care, with caregiver support for safety   |
| Psychosocial Support                | Individual and group therapy sessions (Including therapeutic games, storytelling, friendship enrichment program), health promotion through the health diary IEC material | Breathing exercise and Meditation on daily basis, Psychological Counselling as per the patient's requirement, and Group sessions once in 2-3 month                                                                           | In-person or via tele-health                | Self-care                                      |

Details of the intervention are provided as an additional file.

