## 1 PROTOCOL SUMMARY

### 1.1 SYNOPSIS

**Title:** Effectiveness and Implementation of a Primary Healthcare Intervention for Screening and Management of Multimorbidity and Frailty among Urban Older Adults: The Multi-FrAME Study

**Design:** Phase 3 cluster randomized, parallel arm, observer-blinded trial.

**Objective:** To assess the effectiveness of the Multi-FrAME intervention package in improving health outcomes for older adults with multimorbidity and frailty.

**Setting:** Urban Primary Healthcare Centres (PHCs) in Bhubaneswar, India.

**Participants:** Older adults (aged 60+) with multimorbidity and frailty (Frailty Index  $\geq 25$ ), without dementia, and not bedridden.

**Intervention:** The Multi-FrAME package, which includes medical management, nutritional support, physiotherapy, physical activity, and psychosocial counselling.

**Comparator:** Standard routine care.

**Primary Outcome:** Improvement in health-related quality of life, measured by EQ-5D-5L index scores.

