**Daily Intervention and Health Diary:**

- Each patient will receive a daily administered intervention and a health diary for recording their daily intake or practice of the intervention.
- The health diary will include detail doses, frequency, timing, and other relevant information.
- Participants are required to update the health diary daily.
- Investigators will collect and review health diary data monthly during contact sessions.

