**B. Secondary Endpoints:**

i. **Frailty Index:**

- a. **Tool:** Cumulative Deficit Frailty Index (Rockwood et al., 2005)
- b. **Details of the index:** The study will employ a deficit-based frailty index (FI) to assess frailty status, following the cumulative deficit model (Ghosh et al., 2023). The FI will be constructed using 40 health-related variables covering multiple domains, including chronic diseases, functional limitations, cognitive impairments, and self-perceived health status. Each variable will be coded as 0 (deficit absent), 1 (deficit present), or assigned an intermediate value (e.g., 0.5) for partial deficits. The FI score for each participant will be calculated by dividing the total number of deficits present by the total number of variables assessed, resulting in a score ranging from 0 to 1. Based on this score, participants will be categorized as robust ( $FI \leq 0.15$ ), prefrail ( $FI > 0.15$  to  $\leq 0.24$ ), or frail ( $FI > 0.25$ ). This method provides a comprehensive and standardized approach to measuring frailty by accounting for the accumulation of health deficits across multiple domains.
- c. **Assessment Schedule:** Assessed at baseline, 6, and 12 months.

ii. **ADL/IADL:**

- a. **Tool:** Lawton and Brody Instrumental Activities of Daily Living Scale (Lawton & Brody, 1969)
- b. **Assessment Schedule:** Conducted at baseline, 6, and 12 months.

iii. **Healthcare Utilization:**

- a. **Tool:** Custom questionnaire capturing healthcare visits and hospital admissions.
  - b. **Data Collection:** Monthly via participant health diaries and healthcare records.
- iv. **Healthcare Expenditure:**
  - a. **Assessment:** Monthly data collection from participant reports and receipt submissions.
- v. **Medication Adherence:**
  - a. **Tool:** Medication Adherence Reporting Scale (MARS) (Thompson et al., 2000)
  - b. **Frequency:** Assessed at 0, 6, and 12 months.
- vi. **Patient Satisfaction:**
  - a. **Tool:** Patient Satisfaction Questionnaire (Greenfield & Attkisson, 1989)
  - b. **Frequency:** Evaluated at 6, and 12 months.
- vii. **Mortality Rates:**
  - a. **Data Collection:** Continuous monitoring throughout the study period using health records and family reports.

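### The protocol does not fix which arm receives the Health Diary, which is both a component of the package and a source for an outcome compared between arms

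*Protocol*

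**What the plan says.** The comparator in the synopsis (Protocol 1.1) is "Standard routine care".

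Section 6.2 introduces the diary with "Each participant will receive a 'Health Diary,' serving multiple purposes". Its listed purposes are a log of the intervention, a file for reports and other medicines, and educational content; on the last it says "Contains materials for health promotion, behavior change, and education". The table in 6.2 then places the diary inside the package twice: under Medical Management as "Diary for improving adherence and compliance", and under Psychosocial Support as "health promotion through the health diary IEC material".

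Section 6.3 words the allocation differently: "Each patient will receive a daily administered intervention and a health diary for recording their daily intake or practice of the intervention".

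The diary is also a data source. Section 9.1 B gives the collection of healthcare utilization as "Monthly via participant health diaries and healthcare records", and section 9.3 has participants keep daily logs that are gathered each month for data entry and analysis. Neither section names an arm. Section 12.4.3 compares utilization between the intervention and control groups.

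**The concern.** The diary has two roles that pull in opposite directions. As an adherence aid and carrier of behaviour-change material, it belongs in the intervention arm only. As an outcome source, it is needed in both arms or in neither. The protocol assigns both roles without saying who holds a diary, so two PHCs could apply the text differently and both be following it.

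Two things are at stake. The first is what the control arm represents: routine care, or routine care plus a study-issued adherence and education tool. The second is whether healthcare utilization is measured in the same way in the two arms.

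**Working it through.** **Step 1. Which arm does the text point to?**

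- Pointing to the intervention arm only: the sentence stands in the chapter on the study intervention; the first listed purpose is to log the intervention and help verify fidelity; and section 6.3 issues the diary in the same sentence as the daily intervention, which controls do not receive.
- Pointing to both arms, or silent: the sentence in 6.2 says each participant without restriction; the bullet just before it, on monthly sessions, covers all testing and data collection, which both arms need; section 9.1 uses the diary for a between-arm outcome; section 9.3 has participants in general keep the logs.

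The balance favours intervention-only issue, but the protocol does not settle it.

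**Step 2. Consequence if both arms hold the diary.**

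Controls receive an item that 6.2 lists in two of its four intervention categories. The comparison becomes package against routine care plus diary. Medication adherence is the most exposed outcome, since the diary is listed for that purpose. The sensitivity analysis in 12.4.8 excludes control-arm contamination, meaning interventions that controls receive or take by themselves. It does not clearly cover a diary issued by the study. If every control had one, excluding contaminated controls would leave no comparison group.

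**Step 3. Consequence if only the intervention arm holds it.**

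Utilization is drawn from diary plus records in one arm and without the diary in the other. If a fraction c_I of true events is captured in the intervention arm and c_C in the control arm, then

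observed event ratio = true event ratio × (c_I / c_C).

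The observed ratio equals the true one only when c_I = c_C. A daily diary read monthly is a reason to expect c_I to exceed c_C, which would work against showing the hoped-for reduction. The documents give neither fraction, so the size is unknown.

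**Step 4. Illustration of dilution under Step 2 (the diary share is assumed).**

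The protocol text shown states no final sample size, cluster number or cluster size, so there is no figure of its own to reproduce. Inputs from 12.2: control mean 0.87, SD 0.17, improvement 10%, power 90%, significance level 0.05 (two-sided).

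Difference = 0.10 × 0.87 = 0.087; d = 0.087 / 0.17 = 0.512.

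n per arm = 2 × (1.960 + 1.282)² × 0.17² / 0.087² = 80.2, so 81 before the design effect and attrition (81.2, so 82, by the t-test version).

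Suppose controls gain a share f of the full effect. Contrast = 0.087 × (1 − f); power = Φ(contrast × √(81/2) / 0.17 − 1.960); required n rises by 1/(1 − f)².

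| f (assumed) | Contrast | Power at 81 per arm | n per arm for 90% | Factor |
|---|---|---|---|---|
| 0 | 0.087 | 90.3% | 81 | 1.00 |
| 5% | 0.083 | 87.2% | 89 | 1.11 |
| 10% | 0.078 | 83.4% | 100 | 1.23 |
| 20% | 0.070 | 74.1% | 126 | 1.56 |
| 30% | 0.061 | 62.5% | 164 | 2.04 |

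At a fixed cluster size, the design effect and attrition multiply every n by the same factor, so the last column is unchanged. Nothing in the protocol says which row applies. If controls hold no diary, it is the first.

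**The case against.** A reader might infer that controls certainly receive part of the package and that the EQ-5D-5L effect is therefore diluted. The document does not support that. It nowhere gives controls the diary, and section 6.3 cannot be read across both arms without handing controls the whole intervention. This stands, and it makes the dilution conditional.

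It can also be said that controls need no diary for 9.1 to work. The named tool for utilization is a custom questionnaire, healthcare records are the second source, the Schedule of Activities assesses utilization at 0, 6 and 12 months, and the Follow-up CRF collects it at 6 and 12. This stands in part: the control arm would still have a source. It would still lack one of the two sources named for monthly collection, so the asymmetry between arms remains.

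The annexures (Details of Interventions, Health Diary, CRFs, manual of procedures) are not shown and may settle the matter. The annexure list names one Health Diary and no control version, but its content cannot be judged. Even if an annexure resolves it, the body of the protocol should agree with it.

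Finally, with diaries in both arms the randomised contrast would still be valid for the question of package against routine care plus diary. That is correct, but it is not the question the synopsis poses. Nor do the documents support any particular diary share, so the table above only restates its own input.

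**Conclusion.** The point holds as an unresolved allocation that causes a problem on either reading. With diaries in both arms, the comparator is no longer standard routine care and the contrast may shrink, most directly for medication adherence. With diaries in the intervention arm only, which is the likelier reading, utilization is ascertained differently by arm.

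The size of neither effect can be derived from the documents. The power figures rest wholly on an assumed diary share and on controls holding the full diary, and should not be quoted as an expected loss. It would also go too far to say that a null result would be uninterpretable: that requires both the both-arms reading and a material diary effect, and the protocol establishes neither. This is a worthwhile and cheap correction to make before PHCs apply the text.

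**What to change.** In sections 6.2, 6.3, 9.1 and 9.3, name the arm wherever the diary appears:

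- State that the full Health Diary is issued in intervention PHCs only.
- Capture healthcare utilization in both arms with the same instrument, fields and schedule. One way is a plain record for control participants with outcome fields identical to those in the diary, and no educational, adherence-aid or practice-log content.
- Describe the comparator as routine care plus trial assessments and, if used, the plain record.

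This settles both readings: controls hold no package content, and utilization is recorded alike. The cost is one short extra form and wording changes in four sections. The small downside is that the two booklets look different and could reveal the arm, so participants should be told not to bring them to blinded outcome assessments.
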